| 1. **Study population**   The study period will be from 1st April 2007 to 31st December 2015.  We will perform all analyses in patients that were eligible for all linkages and fulfil the following:   1. registered at a participating English practice prior to the transfer of identifiers to the trusted third party for matching for at least a year before their entry into the study 2. their practice is deemed to be contributing ‘up-to-standard' (UTS) data at study start date 3. they had a valid identifier for linkage (NHS number for ONS mortality and HES data, postcode for IMD) 4. they had not opted out or dissented from CPRD or the linkage scheme 5. individual record is of ‘acceptable' research quality as verified by the CPRD.   **Cohort 1**: Individuals who were registered with a GP contributing to CPRD between 1st April 2007 and 31st December 2015 and who have a complete record on age, gender and IMD are eligible for inclusion in this study (see *P. Plans for addressing missing data*). Patients must have been registered with their GP for at least one year before entering the study with the exception of children aged less than one year who will be assumed to be born into the Practice. Patients can enter the study late or leave the study early in order to include patients who died within the study period (who might be inherently less healthy). Patients enter the study population on the latest of the following dates: continuous registration with GP for 12 months or 1st April 2007. Where patients registered with their GP after the 1st April 2007, patients enter the cohort after 12 months of continuous registration. Patients exit the cohort on the earliest of the following dates: the date the patient died, the date the patient left the practice, or 31st December 2015.  Subsequent studies are nested within cohort 1 (see Error: Reference source not found):   1. Nested cross-sectional study: Patients within cohort 1 with at least one prescription of an antibiotic 2. Nested cohort studies of specific infection syndromes: Patients within cohort 1 with at least one GP consultation for a specific infection syndrome (respiratory, urinary, skin/soft tissue). For these cohorts, patients will enter the cohort on the day of the consultation for infection. Patients will leave the cohort on the earlier of: 28 days after initial consultation, death, transfer out of practice or 31st December 2015. Patients can enter and exit the cohort more than once. |

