| 1. **Data/ Statistical Analysis**   *1. Estimate the incidence of i) GP consultations for infection and ii) antibiotic prescriptions*  For every patient in cohort 1, data on all consultations for infection and antibiotic prescriptions occurring within the study period will be extracted. We will estimate the incidence of GP consultations for infection and antibiotic prescriptions. This will be done for all consultations and prescriptions, and then separately for each category of infection and each class of antibiotics, based on chapter 5.1 of the British National Formulary (BNF) (see Appendix Tables 1 & 2). The denominator will be estimated as total person-time contributed by patients in the cohort during the study period. We will use Poisson regression to estimate the adjusted rate of consultation and prescription, taking account of the effect of age, gender, SES, ethnicity, selected co-morbidity, smoking and obesity. Random effects will be included to take account of clustering of observations by practice. Rates will be assessed for overdispersion by additionally fitting a negative binomial model and testing for alpha greater than zero via a likelihood-ratio test. If rates are found to be overdispersed, the negative binomial model will be used instead of a Poisson model. Adjusted rate ratios will be presented with 95%-confidence intervals.  *2. Describe antibiotic prescribing patterns linked to the reason for prescription*  The overall number of antibiotic prescribing episodes will be calculated for each patient individually, counting all recorded prescriptions between 1st April 2007 and 31st December 2015. For each episode, a clinical indication will be ascertained. Read codes for a diagnosis or symptom of infection recorded on the same day as the antibiotic prescription will be assumed to represent an indication for the prescription. Where more than one possible indication within the same type of infection is recorded on the day of prescription, the more granular code will be used. If multiple indications across different types of infection are recorded, the prescription will be labelled as having multiple indications. Conversely, if no infectious indication for a prescription was found, the prescription will be labelled as having no infectious indication and we will look for any non-infectious codes associated with the date of antibiotic prescription. The ten most common indications will be established and compared to the same numbers for the period from 1998-2001.14 This approach will be replicated for each class of antibiotics based on chapter 5.1 of the BNF. Patterns of repeat consultation or prescription during episodes of infection which may be prolonged will be investigated for each antibiotic prescription extracted in objective 1. We will define a new episode as a consultation or prescription recorded at least 28 days after any previous consultation for infection or antibiotic prescription. We will undertake sensitivity analyses to investigate the impact of using different time periods to define an episode. We will also examine the use of regular (prophylactic) antibiotic treatment.  Proportions and appropriate 95%-confidence intervals will be calculated and all results will be stratified by age-group, gender, SES, ethnicity, selected co-morbidity, obesity and smoking status. Descriptive data will be displayed graphically.  *3. Estimate the incidence of adverse outcomes in the following 28 days*  For each of the selected clinical infection syndromes in the nested cohort study, events in CPRD, HES and ONS will be searched for all adverse outcomes of interest (see *M.* Exposures, Health Outcomes§ and Covariates). Crude incidence rates of for each outcome will be calculated for patients who were treated (exposed) and not treated (unexposed) with an antibiotic. The denominator will be estimated as the total person-time contributed by patients at risk of each adverse outcome, taking account of the fact that this will be different for each outcome. For example, exposed and unexposed patients cannot consult General Practice if they have been admitted to hospital and should therefore not contribute to the denominator during this period when estimating rates of GP re-consultation in the 28 days following consultation for infection. A Poisson regression model will be used to estimate adjusted rates of adverse outcomes in each group, controlling for age, gender, socio-economic status, ethnicity, co-morbidity, obesity and smoking status and assessing for interaction between age and co-morbidity. Random effects will be included to take account of clustering of observations by practice. If the outcomes are overdispersed, negative binomial models will be used instead of Poisson models. Adjusted rate ratios will be presented with 95%-confidence intervals.  *4. Estimate the number of patients needed to treat with antibiotics to avoid one infection-related adverse outcome*  For each clinical infection syndrome-related adverse outcome identified in objective 3, the odds of that outcome in the 28 days following consultation for those treated with antibiotics (unexposed) and not treated with antibiotics (exposed) will be estimated using logistic regression. We will calculate adjusted odds ratios for the protective effect of antibiotics, adjusting for age, gender, SES, ethnicity, year/season, co-morbidity and the probability of receiving antibiotic treatment (see *O. Plan for addressing confounding*) and assessing for interactions with age and co-morbidity. We will use mixed models to adjust for clustering at a practice level and to take account of clustering of observations within a patient due to repeat episodes of infection. Where there is a significant effect of antibiotics between treated and untreated patients, the NNT or NNH to prevent one individual from developing an adverse outcome is calculated as *1/(absolute risk difference)*. A significant effect will be defined by a p-value < 0.05 for the coefficients of antibiotic treatment and its interactions. To avoid an arbitrary cut-off point, p-values close to 0.05 will also be assessed but discussed separately. The NNT will then be used to assess the clinical relevance of any significant differences found. Whilst the relative risk reduction (RRR) may be similar, the NNT may be different due to differing background risk. This will be explored.  *5. Develop risk prediction tools to support clinical decision making*  For each cohort (i.e. for each of the clinical syndromes of UTI, RTI and SSTI), we will develop a logistic regression risk model to predict the risk of adverse outcomes if patients are treated versus not treated with antibiotics. Models will be developed on a random sample of 80% of the observations within a cohort, reserving 20% of the data to estimate the model’s predictive performance.  A negative outcome will be defined as the occurrence of any of the following within 28 days following the index consultation: hospital admission for infection or complication; re-consultation for infection; A&E admission; death. Antibiotic treatment will be defined as a prescription of an antibiotic on the day of consultation for clinical syndrome. Risk factors will be selected based on the analyses outlined in objectives 1-4 and broadly grouped into: socio-demographic variables, co-morbidity and clinical presentation. Biologically plausible interactions between risk factors and age and between risk factors and co-morbidities will be examined.  Whereas age and sex will be forced into the model, other risk factors will be added in order of their significance in objective 4. Risk factors will be kept in the model if they improve the predictive performance of the model as defined by model discrimination and model calibration.17 For example, a risk factor will be used in the model if it improves discrimination and/or calibration. If a variable improves discrimination but reduces calibration, it will still be included in the model, but will be omitted if it increases calibration at the cost of discrimination.  Model discrimination, i.e. the model’s ability to correctly identify patients with and without an outcome, will be estimated using the concordance (c) statistic.18 The c statistic represents the probability that between two randomly chosen patients, one with the outcome and one without, the model assigns a higher score to the patient with the outcome. As a second measure, model calibration will be assessed using the Hosmer-Lemeshow test.18 We will additionally assess model calibration graphically for reasons for poor calibration by comparing the mean observed outcome in deciles of predicted risk. In this calibration plot, the intercept indicates the extent to which predictions are systematically too low or too high, while the slope reflects overfitting of the model.  For each model, we will estimate the internal validity of discrimination and calibration estimates using cross-validation with bootstrap subsampling based on 1000 iterations. In a secondary analysis, we will assess model performance in subgroups by age, sex and co-morbidity.  Finally, we will develop a simplified scoring system using the risk factors in the model,17 assigning the total score to a specific absolute risk of adverse outcomes in the 28 days following consultation, comparing outcomes if an individual is treated versus not treated with antibiotics. We will assess the predictive performance of the risk scores using the approaches outlined above. |

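### Step 4 models 28-day yes/no outcomes although section K allows follow-up to end sooner, and it sets no rule for shortened episodes or for death and admission before re-consultation

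*Protocol*

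**What the plan says.** Section K (Study population) sets the exit rule for the three nested infection cohorts. Patients leave at the earliest of "28 days after initial consultation, death, transfer out of practice or 31st December 2015". An episode can therefore have less than 28 days of follow-up.

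Section N (Data/Statistical Analysis), step 3, takes account of this: "The denominator will be estimated as the total person-time contributed by patients at risk of each adverse outcome". Its example is that "exposed and unexposed patients cannot consult General Practice if they have been admitted to hospital and should therefore not contribute to the denominator" for re-consultation. The exclusion lasts only while the patient is in hospital.

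Step 4 takes the outcomes of step 3 one at a time and changes the measure to "the odds of that outcome in the 28 days following consultation", which "will be estimated using logistic regression". It then states that "the NNT or NNH to prevent one individual from developing an adverse outcome is calculated as" one over the absolute risk difference. Section M lists the outcomes as separate analyses: re-consultation for the same infection, re-consultation for a side effect, complications, A&E admission, all-cause hospitalisation and all-cause mortality.

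Step 5 also uses logistic regression over 28 days, on a composite of admission for infection or complication, re-consultation for infection, A&E admission and death. Section P (missing data) deals with covariates only.

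**The concern.** A plain logistic model has no person-time, so it cannot carry the at-risk rule of step 3. Unless a further rule is stated, an episode that is not seen to day 28 enters as a non-event for whatever was not observed. There are two separate problems:

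- **Truncation.** Episodes that start in the last 28 days of the study, or are cut by transfer out, have an incomplete window.
- **Competing events.** A patient who dies can no longer re-consult or report a side effect, and a patient in hospital cannot do so for that time. The re-consultation and side-effect risks then depend partly on how often patients are admitted or die.

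The second problem matters because the study compares NNTs between age and co-morbidity groups, which can be expected to differ in admission and death. A difference in the re-consultation NNT could then partly reflect those events.

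**Working it through.** **Inputs.** From section I: OR for antibiotics 0.69, and outcome risk 2.4% (the published pneumonia risk, used there as a stand-in for the study's outcomes). From section K: study period 1 April 2007 to 31 December 2015. Assumed, because the protocol gives no figure: transfer out 5% to 15% a year, the unequal exit shares, a 15% re-consultation risk and an 8% admission risk.

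**1. The plan's own figure.** With untreated risk p0 = 0.024 and OR 0.69, the treated odds are 0.024/0.976 × 0.69 = 0.01697, so p1 = 0.01668. With an assumed 80% treated, the Wald formula N = (1.960 + 0.842)² × [1/(0.2 × p0(1−p0)) + 1/(0.8 × p1(1−p1))] / (ln 0.69)² gives 16,511, against 16,512 in section I. The same formula at 0.04% risk gives the stated 971,057. The plan's sample sizes thus also assume a plain binary outcome. The reference NNT is 1/(0.02400 − 0.01668) = 136.7.

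**2. Study end.** The period has 3,197 days. Index dates from 4 to 31 December 2015 cannot reach day 28. That is 28 days, and 28/3,197 = 0.88% of episodes if consultations are evenly spread.

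**3. Transfer out.** The share of episodes cut within 28 days is 1 − (1 − t)^(28/365.25), where t is the yearly transfer rate. This gives 0.39% for t = 5% and 1.24% for t = 15%. With study end, the total is about 1.3% to 2.1%.

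**4. Equal truncation in both groups.** If a share c leaves uniformly over the window and is coded event-free, each risk is multiplied by (1 − c/2). At c = 1.25% the NNT moves from 136.7 to 137.5 and the OR stays at 0.690. At c = 2.12% the NNT is 136.7/(1 − 0.0106) = 138.2.

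**5. Unequal exit (assumed shares, same formula, risk 2.4%).** Section O expects higher-risk patients to be treated more often, so early exit may be commoner in the treated.

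| OR | Exit, untreated / treated | True NNT | Observed NNT |
|---|---|---|---|
| 0.69 | 2% / 5% | 136.7 | 133.5 |
| 0.69 | 2% / 10% | 136.7 | 126.4 |
| 0.90 | 2% / 5% | 425.9 | 377.5 |
| 0.90 | 2% / 10% | 425.9 | 313.4 |

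The NNT falls by 2% to 26%, so antibiotics look more protective.

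**6. The opposite direction.** Suppose instead that antibiotics prevent admissions, so that more untreated patients lose the chance to re-consult. With re-consultation risk 15% and OR 0.69, the risk difference is 0.0415 (NNT 24.1). Prevented admissions are 0.0073 at 2.4% admission risk (the section I figure, used here by assumption) and 0.0234 at 8%. Let a share s of these patients be ones who would otherwise have re-consulted, and subtract s times the prevented admissions from 0.0415:

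| Admission risk | NNT, s = 15% | NNT, s = 100% |
|---|---|---|
| 2.4% | 24.8 | 29.3 |
| 8% | 26.4 | 55.4 |

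Here antibiotics look less protective. The s = 100% column is an extreme bound: it needs every prevented admission to displace a re-consultation, with none seen before admission or after discharge.

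**The case against.** The strongest reply has five parts.

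- **Nothing says that shortened episodes are coded as non-events.** This is correct. Such coding is only the default of a plain 28-day logistic model, and exclusion, censoring or weighting could be left to an analysis plan that is not shown. What remains is a conflict within the protocol: it fixes variable follow-up, an at-risk rule in step 3 and a fixed-window model in step 4, and does not reconcile them.
- **Admitted patients are not lost for good.** This stands. Step 3 removes them only while in hospital, and a re-consultation before admission or after discharge within 28 days still counts.
- **Rates in step 3 and risks in step 4 need not agree.** This also stands. Section O describes objectives 1 to 3 as descriptive. A 28-day risk that counts death as no re-consultation is a valid cumulative incidence. The difficulty is reading its NNT as benefit without saying so.
- **Severely ill patients do appear as events.** Hospitalisation, A&E admission and death are each analysed in their own right.
- **Objective 5 is largely protected.** A reader might infer that steps 4 and 5 share the fault equally. The protocol does not support that: the step 5 composite counts death, A&E admission and admission for infection or complication as events, and does not include side effects.

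A reader might also infer that the benefit of antibiotics is always understated, perhaps by half. The protocol supports neither. Parts 5 and 6 of the check point in opposite directions, and the large figure needs extreme assumed inputs.

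**Conclusion.** The point holds for objective 4, chiefly for the two re-consultation outcomes, whose NNT as written does not follow the at-risk rule of step 3. Truncation is minor: about 0.9% of episodes from study end, assuming an even spread of consultations, plus an assumed 0.4% to 1.2% from transfer out. It has almost no effect on the NNT if equal in both groups. Death and admission can have a larger effect where admission risk is high, but neither size nor sign can be settled from the protocol. Objective 5 is affected only by transfer out, study end and admissions for other causes. This is a cheap improvement, and it does not show the main results to be invalid.

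**What to change.** 1. In section K, admit index consultations to the nested cohorts only up to 3 December 2015, so that every episode has a possible 28-day window.
2. In steps 4 and 5, treat episodes cut by transfer out as censored (for example by inverse-probability-of-censoring weighting) or exclude them, and do not count them as event-free. Follow outcomes taken from HES or ONS to day 28 where the linked data cover that time. For outcomes drawn from several sources, such as complications, state which follow-up applies.
3. In step 4, keep re-consultation and side effects as separate outcomes. State that their 28-day risks are cumulative incidences with death and admission as competing events, and whether a re-consultation after discharge counts.
4. Add a sensitivity NNT for re-consultation, admission or death within 28 days, with its components shown, so that co-morbidity differences are not read from re-consultation alone. Replacing the re-consultation outcome with this composite would be a debatable choice of estimand, so it should be an added analysis only.

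The cost is about 1% of episodes at the end of the period, some protocol wording and modest extra programming.

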| 1. **Objectives, Specific Aims and Rationale**   *Objective*  To investigate the use of antibiotics and their protective effect against complications of infection to inform the development of risk prediction models to guide antibiotic treatment decisions for suspected infection in primary care.  *Aims*   1. Estimate the incidence of i) GP consultations for infection and ii) antibiotic prescriptions by: age-group, gender, SES, ethnicity, selected co-morbidities, obesity and smoking status 2. Describe antibiotic prescribing patterns linked to the reason for the prescription by: age-group, gender, SES, ethnicity, selected co-morbidities, obesity and smoking status 3. Estimate the incidence of adverse outcomes in the following 28 days including: hospital admission for infection; A&E admission; re-consultation for infection; re-consultation for antibiotic side-effects (rash, nausea, …) and death for patients with a GP consultation for i) respiratory tract infection ii) urinary tract iii) skin/soft tissue infection, comparing patients with each listed age/co-morbidity group (including smoking status and obesity) to non-comorbid patients 4. Estimate the number of patients needed to treat with antibiotics to avoid one infection-related adverse outcome, comparing the results for each age/co-morbidity group to non-comorbid patients 5. Develop risk prediction tools to support clinical decision making and communication with patients   *Rational*  We have previously shown that more than half of all antibiotic prescriptions in primary care are issued to less than 10% of patients, and that this 10% of patients have high levels of co-morbidity.1 Targeting such high-frequency users of antibiotics in antimicrobial stewardship programmes might provide opportunities for a more effective intervention approach. Underlying this hypothesis is the assumption that it might be safe and feasible to reduce prescribing in patients with the highest levels of antibiotic prescribing, many of whom have co-morbidity.  To investigate whether higher rates of antibiotic use are likely to be justified in higher risk patients compared to patients who lack these risk factors, we will undertake a series of studies to investigate which patients in terms of age, gender, SES, ethnicity, selected co-morbidities, obesity and smoking get the most antibiotics. We will determine which patients are most likely to receive antibiotics for which infections and relate this to national guidance on antibiotic prescribing. To estimate whether the protective effect of antibiotics differs according to the patient’s age and the presence of co-morbidity, obesity or their smoking status, we will estimate the risk of infection related adverse-outcomes, comparing patients who have been treated with antibiotics to those who have not been treated with antibiotics for each of these groups. We will use these estimates to calculate the number of patients who need to be treated with antibiotics to avoid one infection-related adverse outcome (NNT), accounting for age, gender, SES, ethnicity, co-morbidity, obesity and smoking status. This will inform the development and validation of individualised risk-prediction models to support clinical decision-making and patient communication around the need for antibiotic treatment for suspected infection in primary care. |

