| 1. **Study Design**   For this study, we will use a retrospective cohort study design, looking at patients with consultations for infection and/or antibiotic prescribing between 1st April 2007 and 31st December 2015. (for an exact definition see *K. Study population* and *Error: Reference source not found*)  In a first step (Objective 1), we will describe the incidence of GP consultations for infection and the incidence of antibiotic prescribing in the main study population. This will provide important context on the burden of infection and frequency of antibiotic use in primary care.  Within the main study population, we will then undertake a nested cross-sectional study looking at all antibiotic prescriptions in the main study population. For each prescription we will use Read codes on the day of the prescription to establish the reason for the prescription. (Objective 2) This will inform our understanding of why antibiotics are prescribed.  Next, we will undertake a series of cohort studies focused on specific infectious syndromes within the main population. Three nested cohorts will be built based on a GP consultation for a) respiratory tract infection, b) urinary tract infection and c) skin/soft tissue infection. For each cohort, we will estimate the rate of infection-related adverse outcomes within 28 days of the initial GP consultation for patients with and without antibiotic treatment. (Objective 3)  In order to determine the protective effects of antibiotics against these adverse outcomes, we will then estimate the Number Needed To Treat with antibiotics (NNT) to prevent one additional adverse outcome. In particular, we will compare the NNT for patients with and without co-morbidities of interest, obesity or smoking. (Objective 4).  Finally, we will synthesize out analyses in objectives 1-4 to develop a risk model for each cohort (respiratory, urinary and skin/soft tissue models). These models will support clinical decisions and patient communication around the need for antibiotic treatment for suspected infection (Objective 5).  Results across all steps will be stratified or adjusted by age, gender, SES, ethnicity, co-morbidity, obesity and smoking status. |

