| 1. **Data Linkage Required (if applicable):§**   **§***Please note that the data linkage/s requested in research protocols will be published by the CPRD as part of its transparency policy*  The study will make use of linked data, which will consist of linked CPRD, Office of National Statistics (ONS) mortality and Index of Multiple Deprivation (IMD) and Hospital Episode Statistics (HES) inpatient and A&E datasets. CPRD data will be obtained through the existing UCL institutional licence and up-to-date HES/ONS datasets will be obtained by making an appropriate request to CPRD.  Information in inpatient and A&E HES will be utilised to identify hospitalisation after presentation in primary care.  ONS data will be used as the source to a) determine death dates, and b) obtain and include social deprivation as a covariate in our models. |

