| 1. **Exposures, Health Outcomes§ and Covariates**   **§***Please note:**Summary information on health outcomes (as included on the ISAC application form above) will be published on CPRD’s website as part of its transparency policy*  *Exposure*  Exposures will include i) prescription of an antibiotic ii) GP consultation for suspected infection (see Appendices: Table 1 – Codelist for antibiotics, Table 2 – Codelist categorising indications for antibiotic use and Table 3 – Codelists to identify patients with suspected respiratory tract, urinary tract or skin/soft tissue infection)  *Health Outcomes*  The following outcomes (within 28 days of presentation in primary care) will be separately considered for analysis:   - Re-consultation for the same type of infection (CPRD; see Appendix Table 3) - Re-consultation for a side effect of antibiotic treatment (CPRD; see Appendix Table 4a –side effects of antibiotic treatment) - Complications of infection in primary or secondary care (CPRD and inpatient HES; see Appendices: Table 4b and 4c – complications of infection; depending on the indication) - Admission to Accident & Emergency (HES A&E) - All-cause hospitalisation (inpatient HES) - All-cause mortality (CPRD, HES and ONS)   We will undertake a sensitivity analysis to investigate the impact of excluding outcomes that occur on the same day as the exposure. The impact of different time windows will be explored, informed by a literature review on the natural history of the duration of different infections.  *Covariates*  We will include the following covariates:   - Age (classified as 0-4, 5-17, 18-44, 45-64, 65-84, 85-94 and 95+, years of age inclusive) - Sex (female and male) - Index of Multiple Deprivation (IMD; 1-5) - Co-morbidities (coded as indicator variables based on national guidance from Public Health England3 and feasibility1; see Appendix Table 5 for comorbidity code list)   - Diabetes   - Chronic Kidney Disease (CKD)   - Chronic Obstructive Pulmonary Disease (COPD)   - Asthma - Obesity - Smoking status15 - Season (months or quarters) and year - Ethnicity   We will undertake a sensitivity analysis of the impact of coding co-morbidities as binary indicator variable and as total number of co-morbidities. |

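### Antibiotic side effects are sought only as GP re-consultations, so reactions managed only in hospital, or fatal, cannot enter the study's one specific harm outcome

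*Protocol*

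**What the plan says.** The Health Outcomes list in section M (Exposures, Health Outcomes and Covariates) gives each outcome its own data source. For harm it reads "Re-consultation for a side effect of antibiotic treatment (CPRD; see Appendix Table 4a". The next item is "Complications of infection in primary or secondary care (CPRD and inpatient HES; see Appendices: Table 4b and 4c". The list ends with three outcomes that carry no restriction on cause: "Admission to Accident & Emergency (HES A&E) - All-cause hospitalisation (inpatient HES) - All-cause mortality (CPRD, HES and ONS". Aim 3, in Objectives, Specific Aims and Rationale, frames harm the same way as section M: "re-consultation for antibiotic side-effects (rash, nausea".

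The hospital data are already part of the request. The data linkage section states: "Information in inpatient and A&E HES will be utilised to identify hospitalisation after presentation in primary care".

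Two places describe the outcome set as a whole. The Study Design section says "we will estimate the rate of infection-related adverse outcomes within 28 days of the initial GP consultation". Section N (Data/Statistical Analysis), step 4, opens with "For each clinical infection syndrome-related adverse outcome identified in objective 3" and then states that "the NNT or NNH to prevent one individual from developing an adverse outcome is calculated as" the reciprocal of the absolute risk difference.

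**The concern.** The study is meant to inform decisions about who needs an antibiotic, and it names side effects as an outcome alongside the outcomes that antibiotics may prevent. The two sides are not ascertained alike. A complication of infection can be found in the GP record or the inpatient record. A side effect can be found only if the patient goes back to the GP. The definition therefore favours reactions mild enough to be taken to the GP and leaves out those that go straight to hospital, or that are fatal, without a GP re-consultation.

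Two things are at stake. First, the NNH for side effects would describe only reactions seen in general practice, and a reader could take it for the harm of treatment as a whole. Second, the hospital-managed reactions reappear, unidentified, in outcomes that the protocol calls infection-related, so the NNTs for those outcomes could be misread as measuring protection against infection alone.

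**Working it through.** The protocol states no figure on this point, so there is nothing to reproduce. The check compares definitions.

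**1. What each outcome can capture.** Take a patient who has a serious reaction to an antibiotic within 28 days of the index consultation, is managed only in hospital or dies, and does not re-consult the GP about it.

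| Outcome in section M | Source | Can this event count? |
|---|---|---|
| Side effect of treatment | CPRD re-consultation | No |
| Complication of infection | CPRD and inpatient HES | Only if the complication lists happen to include the code |
| A&E admission | HES A&E | Yes, if the patient went through A&E |
| All-cause hospitalisation | Inpatient HES | Yes, if admitted |
| All-cause mortality | CPRD, HES and ONS | Yes, if fatal |

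The event can therefore be counted, but not as a side effect.

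**2. Whether other text closes the gap.** Section N, step 3, says that CPRD, HES and ONS will be searched for the adverse outcomes, but it points back to section M for what those are, and section M names CPRD alone for side effects. The code list in Appendix Table 4a is not shown. It cannot widen the outcome to hospital in any case, because section M fixes both the event type (re-consultation) and the source (CPRD). Step 3 also removes time in hospital from the denominator when rates of GP re-consultation are estimated. An admitted patient then contributes neither a side-effect event nor person-time to that outcome during the stay. The Limitations section mentions incomplete A&E coverage and general coding misclassification, but not this gap.

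**3. Direction of the effect on the NNH.** Let r1 and r0 be the side-effect risks recorded in treated and untreated patients, and m1 and m0 the additional risks of reactions that never reach the GP.

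- Recorded NNH = 1/(r1 − r0)
- NNH with all reactions counted = 1/[(r1 + m1) − (r0 + m0)]

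Where r1 exceeds r0, the recorded NNH is too large whenever m1 exceeds m0. Antibiotic reactions need exposure to an antibiotic, so m1 > m0 is the natural expectation, though it remains an assumption. The protocol gives none of the four quantities, so the direction can be stated but not the amount.

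**4. Effect on the hospital and death outcomes.** In an all-cause outcome a reaction in a treated patient adds to the treated risk, and the treated-versus-untreated contrast nets it against any protection. That is a correct estimate of the net effect. Only the label is at fault: such an NNT is not the number needed to avoid one event caused by infection.

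**The case against.** The strongest reply is that the protocol is consistent. Aim 3 and section M both define a primary-care endpoint, and an NNH for that endpoint is valid for what it measures. The main effects of interest, according to the sample size section, are the protective effect of antibiotics and its interaction with co-morbidity; no formal weighing of benefit against harm is promised. This stands as far as it goes: there is no contradiction over side effects. It does not remove the gap, because this is the only outcome specific to drug harm, and the limit on what it can see is stated nowhere.

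It is also fair that a patient who later re-consults the GP about the reaction within 28 days is captured, so the gap is confined to those who do not.

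A reader might infer more: that serious reactions are counted as complications of infection and so bias the NNTs by a calculable amount. The document does not support this. Section M considers each outcome separately, and the reactions enter through outcomes with no cause restriction, where they belong. Whether the complication lists contain reaction codes cannot be seen.

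Nor can a size be given. The sample size section's 2.4% risk and odds ratio of 0.69 can be combined: treated odds = 0.69 × 0.024/0.976 = 0.01697, treated risk 1.668%, risk difference 0.732 points, NNT 137. Adding an assumed risk h of a hospital-managed reaction, with treated risk = 0.01668 + h(1 − 0.01668), gives an NNT of 139 for h = 0.01% and 187 for h = 0.2%. But h is invented, 2.4% is a pneumonia risk, and 0.69 is an average across complications. The shift is also not an error in an all-cause outcome. These figures show only that the answer depends on the assumed h.

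Finally, the two consequences do not point the same way. Understated side effects flatter antibiotics, while reading a net NNT as pure protection makes antibiotics look less protective than they are.

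**Conclusion.** The concern holds in a limited form. Followed as written, section M leaves out of the side-effect outcome every reaction that is managed only in hospital, or is fatal, without a GP re-consultation within 28 days. The side-effect rate is then understated. Its NNH looks too favourable, on the assumption that such reactions are commoner in treated than in untreated patients. A&E admission, all-cause hospitalisation and all-cause mortality remain valid as net outcomes; what needs correcting there is their description as infection-related in the Study Design section and in step 4. The size cannot be derived from the document, and no percentage error in any NNT should be claimed. This is a worthwhile and cheap improvement to one outcome definition and to the wording around others. It does not threaten the main comparison.

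**What to change.** In section M, and correspondingly in aim 3, redefine the outcome as *side effect of antibiotic treatment in primary or secondary care (CPRD and inpatient HES)*. Add an ICD-10 list of adverse drug reaction codes to the appendix and apply it identically to treated and untreated patients. Report the result as a separate harm outcome in objectives 3 and 4. Leave A&E admission, all-cause hospitalisation and all-cause mortality as they are, and describe their NNTs in the Study Design section and step 4 as net effects of treatment rather than as infection-related.

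The cost is one more code list, run on inpatient HES data that are already requested, and a few changes of wording. The drawback is specificity: some reaction codes do not name the drug, so reactions to other drugs will be included in both groups. Inpatient HES would still miss reactions seen only in A&E and deaths without an admission, so the Limitations section should say so in one sentence.
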